#### Microbial and statistical analyses

2.9.8

Metagenomic sequencing data will be processed with bioBakery workflows using docker images available at http://huttenhower.sph.harvard.edu/biobakery_workflows. Briefly, sequence data quality control, including removal of any human reads, will be conducted using KneadData. Taxonomic and functional profiles of the microbiota will be generated using MetaPhlAn v2.6^[52]^ and HUMAnN2^[53]^ respectively. Strain-level taxonomic profiling will be achieved by SNP haplotype based profiling using StrainPhlAn software.^[54]^ The resulting SNP haplotypes will be used to identify the proportion of shared and unrelated strains between mother-baby pairs, comparing these proportions across treatment groups.

Permutational multivariate analysis of variance (PERMANOVA) will be used to identify any significant differences in the overall microbial community structure between treatment groups. Additionally, Multivariate Association with Linear Models (MaAsLin2) will be used to identify any significant associations between specific microbial taxa and treatment groups. Both taxonomic and functional profiles will be compared. Microbiota stability across time points will be assessed using Bray Curtis dissimilarity. Microbial alpha diversity will be assessed using Shannon's diversity index and gene counts.

Treatment evaluation on clinical outcomes will be performed on the basis of intention to treat, using data collected from all randomized participants. Generalized linear regression models will be used to assess treatment effects, adjusting for sex. Model-adjusted estimates and the difference among the three groups will be calculated and tested. Planned subgroup analysis by sex may be conducted on secondary outcomes to evaluate the consistency of possible treatment effects in males and females. Analyses of non-microbiome data will be performed in SAS v9.4, SPSS v26, and/or Minitab v16. Statistical tests will be two-tailed and significance maintained at 5% level.

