### Outcomes

2.4

Primary outcome:

Difference in the community structure of the gut microbiota between CS groups at 1 month of age.

Secondary outcomes:

Difference in the overall gut microbiota community between CS groups at 24 hours and 3 months of age.Similarity of CS seeded and placebo gut microbiota profiles to those born vaginally at 24 hours, 1 and 3 months of age.Degree of maternal vaginal bacterial strain transfer in CS-born babies at 24 hours, 1 and 3 months of age.BMI *z*-score at 1 and 3 months of age.Total body fat percentage from whole-body dual-energy absorptiometry (DXA) at 3 months of age.

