#### Neonatal assessments

2.9.5

Neonatal assessments differ according to participant study group (CS vs vaginal birth). Post-treatment neonatal clinical assessments are performed only on babies born by CS. A member of the study team records birth weight, length, head circumference, abdominal circumference, and chest circumference measurements for all CS-born babies. These measurements are taken using the weighing scales and tape measures in the hospital where participants give birth. Other neonatal clinical information is also recorded by a research clinician for CS-born babies (e.g., Apgar scores, breastfeeding initiation, and skin-to-skin start time).

Neonatal clinical information for vaginal-born babies are obtained from medical records. Note that abdominal and chest circumference measurements at birth are not recorded for vaginal-born babies as these are not standard measurements, and it is not feasible to have a member of the study team present at these births.

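### BMI z-score and body fat are adjusted for sex only; one prespecified birth-size covariate would probably sharpen the randomized comparison at small cost

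*Protocol article*

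**What the plan says.** Under Microbial and statistical analyses (2.9.8), the protocol article sets the clinical analysis: "Treatment evaluation on clinical outcomes will be performed on the basis of intention to treat, using data collected from all randomized participants". It then gives the model: "Generalized linear regression models will be used to assess treatment effects, adjusting for sex". The next sentence extends the model to the vaginal-born reference group: "Model-adjusted estimates and the difference among the three groups will be calculated and tested".

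The clinical outcomes concerned are listed among the secondary outcomes (2.4): "BMI *z*-score at 1 and 3 months of age" and "Total body fat percentage from whole-body dual-energy absorptiometry (DXA) at 3 months of age".

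Neonatal assessments (2.9.5) shows which birth measurements exist. For the randomized babies, "A member of the study team records birth weight, length, head circumference, abdominal circumference, and chest circumference measurements for all CS-born babies". On instruments: "These measurements are taken using the weighing scales and tape measures in the hospital where participants give birth". For the reference group, "Neonatal clinical information for vaginal-born babies are obtained from medical records".

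The article nowhere adjusts for birth size, explains its absence, or gives a correlation between birth size and these outcomes.

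**The concern.** Birth weight and length give the pre-treatment value of BMI, and birth weight is a natural predictor of later body composition. Both are in hand for the randomized babies, yet the only covariate named is sex. If the z-score reference is sex-specific (the article does not say which reference is used), the z-score has already removed most of the sex effect, and the sex term then does little for BMI. That remark does not apply to fat percentage.

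The design does not balance birth size either. Randomization, allocation, and blinding (2.8) describes computer-generated 1:1 allocation and names no stratification within the CS group. With 15 babies per arm, any outcome variation that birth size could explain stays in the residual and widens the confidence interval. At stake is the precision of the growth and body-composition comparisons, not their validity.

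**Working it through.** **Inputs from the document.** 30 randomized babies, 15 per arm, and 15 vaginal-born babies (2.6); two-sided tests at 5% and sex as covariate (2.9.8). The power statement in 2.6 concerns the primary microbiota outcome. No SD, effect size or power is stated for BMI z-score or fat percentage, so there is no figure of the plan's own to reproduce here.

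**Assumptions.** Normal linear model, no dropout, birth size unaffected by treatment. rho is the correlation of birth size with the outcome given sex; it is not documented, so a range is shown. SD means the outcome SD given sex.

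**Variance, two CS arms.** Treatment plus sex leaves 30 - 3 = 27 residual degrees of freedom. Adding p birth-size covariates multiplies the variance of the treatment effect by

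(1 - rho²) × (27 - 1)/(27 - p - 1).

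The second factor is the cost of estimating the covariate effect: 26/25 = 1.04 for p = 1 and 26/24 = 1.083 for p = 2.

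**Power for a 1 SD difference.** Noncentral F with noncentrality 1²/(2/15) = 7.5 divided by the variance ratio, on 27 degrees of freedom (sex only) or 26 (one covariate). The sex-only model gives 75%, and its difference detectable with 80% power is 1.06 SD.

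| rho | Variance ratio, p = 1 | Power, 1 SD | Detectable at 80% (SD) |
|---|---|---|---|
| 0 | 1.00 × 1.04 = 1.04 | 73% | 1.08 |
| 0.2 | 0.96 × 1.04 = 1.00 | 75% | 1.06 |
| 0.3 | 0.91 × 1.04 = 0.95 | 77% | 1.03 |
| 0.5 | 0.75 × 1.04 = 0.78 | 85% | 0.94 |
| 0.6 | 0.64 × 1.04 = 0.67 | 90% | 0.87 |

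**Break-even.** One covariate: rho² = 1 - 25/26 = 0.038, so rho is about 0.20. Two covariates: rho² = 1 - 24/26 = 0.077, so rho (now a multiple correlation) is about 0.28. With two covariates at 0.3 the ratio is 0.91 × 1.083 = 0.99, almost no gain.

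**Simulation check.** 6,000 trials per value of rho, one covariate: confidence interval width relative to sex only was 1.02, 1.00, 0.97, 0.88 and 0.82 for rho 0, 0.2, 0.3, 0.5 and 0.6. The square roots of the variance ratios are 1.02, 1.00, 0.97, 0.88 and 0.82. Simulated power was up to about 3 points lower than the table for both models. The formula leaves out the cost of chance imbalance in sex, which is common to both; a factor of 27/26 for it takes 75% to 74%.

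**All three groups in one model.** 45 - 4 = 41 residual degrees of freedom, so the cost factor is 40/39 = 1.026. Break-even rho² is 0.025, and at rho 0.5 the ratio is 0.75 × 1.026 = 0.77.

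**The case against.** Nothing in the plan is invalid. Sex-only adjustment of a randomized comparison is unbiased with correct type I error, and a full analysis plan that is not shown might add covariates. The first part stands in full. The second stands only in part, because the article does not leave the matter open: it names a covariate, and names only that one.

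The gain rests on an undocumented correlation. Birth length is taken with hospital tape measures, whereas follow-up length is the median of three neonatometer readings (2.9.6). BMI divides by squared length, so that error weakens birth BMI as a covariate. The correlation may also differ between BMI z-score and fat percentage, and between 1 and 3 months. This stands, and is why a range is shown.

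Three stronger readings are tempting, and the document supports none of them.

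- *Adjustment is free.* A reader might take 15/(1 - rho²) and conclude that the arms grow to 16.5 to 23 babies at rho 0.3 to 0.6. That omits the 26/25 factor. Net of it the equivalents are 15/0.946 = 15.9 and 15/0.666 = 22.5, and below rho of about 0.20 adjustment loses slightly.
- *The unadjusted result contains a spurious effect.* The SD of the chance imbalance between arms is sqrt(2/15) = 0.37. At rho 0.3 to 0.6, some 0.11 to 0.22 SD of it carries into the contrast. This is ordinary sampling error, already inside the confidence interval half-width of about 0.75 SD. It is not bias.
- *The data are at hand for all three groups.* This is shown only for the CS arms. Vaginal-born babies' neonatal information comes from medical records, and birth length is not explicitly listed for them. Birth size may be a confounder in that non-randomized comparison, but the article does not show that the same covariate can be built there.

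**Conclusion.** The point holds as a modest efficiency improvement. The article fixes sex as the only named covariate for BMI z-score and fat percentage and leaves unused a pre-treatment measure recorded for every CS baby. The trade favours adjustment: if birth size is unrelated to the outcome, power for a 1 SD difference falls by about 2 points; at rho 0.5 it rises by about 10, and at 0.6 by about 15. At rho 0.3 the gain is only about 2 points.

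The direction is likely, but the size is uncertain because rho is assumed. Even with a strong covariate the trial detects only large differences (0.87 SD at rho 0.6). The outcomes are secondary in a pilot whose objectives (1.2) concern the gut microbiota, and the primary outcome is untouched.

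**What to change.** In 2.9.8, change 'adjusting for sex' to 'adjusting for sex and one prespecified birth-size covariate', and name it per outcome: birth BMI z-score for BMI z-score at 1 and 3 months, birth-weight z-score for DXA fat percentage at 3 months. Apply this at least to the randomized CS comparison. Extend it to the three-group comparison only if the medical records supply the needed measurements for vaginal-born babies.

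Use one covariate per model rather than entering weight and length separately, since two raise the break-even correlation from about 0.20 to about 0.28. Fix the choice before unblinding; adding it after an imbalance has been seen would make the adjustment data-driven.

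The cost is one line of text, one degree of freedom, and a variance about 4% larger if birth size proves unrelated to the outcome. No new data collection is needed in the CS arms.

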### Interventions

2.3

Eligible babies in the elective CS group are randomized in a 1:1 ratio to receive either active treatment (3 ml vaginal bacteria supernatant) or placebo (3 ml sterile water). A folded 13 × 300 mm sterile gauze with an x-ray strip (Propax, New Zealand) is inserted into the lower vagina of women in the CS group and removed after approximately 30 minutes, as close as possible to their surgery. Women can choose to insert and/or remove the gauze themselves, or have these tasks performed by a clinical member of the research team. Sterile gloves are worn during insertion and removal of the gauze. A counter-signed study swab-count sticker is used to verify the removal of the swab prior to surgery, and added to the woman's clinical notes.

After removal, the gauze is vertically cut into two equal sized pieces using sterile scissors. One piece is kept on ice in a sterile container for transportation back to the Liggins Institute laboratory. The other piece is placed in a sterile syringe with 5 ml of sterile water and mixed to obtain a vaginal bacteria supernatant. Next, 3 ml of this supernatant is transferred to a 3 ml sterile syringe in preparation for oral administration to babies randomized to receive active treatment. The remaining 2 ml of supernatant are transferred to a microcentrifuge tube and stored on ice for transportation back to the laboratory, for later microbiota assessment. If a baby is randomized to receive placebo, only 3 ml of sterile water is placed in the syringe, while the prepared vaginal supernatant is reserved solely for microbiota assessment.

If the attending clinician assesses the newborn as healthy, a member of the research team uses the pre-filled syringe to orally administer either active treatment (3 ml vaginal bacteria supernatant) or placebo (3 ml sterile water). Administration occurs as soon as possible after birth (no later than one hour). Babies in the vaginal-born reference group are not randomized, as no administration of active treatment or placebo occurs in this group.

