### Sample size

2.6

We intend to randomize 30 healthy babies in the CS group on a 1:1 basis to intervention or placebo (15 per group). A power calculation indicated that 15 babies per CS group would be sufficient to detect a moderate effect size of 0.25 standard deviations for our primary outcome (power calculation for balanced one-way ANOVA test, 85% power, α = 0.05). In addition, we intend to recruit 15 babies born vaginally as a reference group.

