### Randomization, allocation, and blinding

2.8

Healthy CS-born babies are randomized in a 1:1 ratio to either treatment or placebo group, using computer-generated randomization. Mothers of randomized babies were blinded to group allocation; the researchers analyzing the primary outcome data, are blinded to baby group (active treatment, placebo, or vaginal-born reference group). For pragmatic reasons, it is not possible for the researcher administering the intervention to be blinded, as they are the only member of the research team present at a woman's CS. Participant un-blinding during the study is permissible in the case of any serious adverse events and upon recommendation by the study's independent data monitoring committee (DMC).

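### The clinical treatment evaluation is limited to randomised babies, yet its only named test spans three groups including the non-randomised reference, and seeded versus placebo is not named as the treatment test

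*Protocol article*

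**What the plan says.** The last paragraph of Microbial and statistical analyses (2.9.8) makes four relevant statements, in this order.

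- Population: "Treatment evaluation on clinical outcomes will be performed on the basis of intention to treat, using data collected from all randomized participants".
- Model: "Generalized linear regression models will be used to assess treatment effects, adjusting for sex".
- Tested quantity: "Model-adjusted estimates and the difference among the three groups will be calculated and tested".
- Level: "Statistical tests will be two-tailed and significance maintained at 5% level".

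Randomization, allocation, and blinding (2.8) shows which three groups are meant, when it says the analysts of the primary outcome are "blinded to baby group (active treatment, placebo, or vaginal-born reference group". Interventions (2.3) settles the status of the third: "Babies in the vaginal-born reference group are not randomized, as no administration of active treatment or placebo occurs in this group".

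Sample size (2.6) plans 15 babies in each caesarean arm and 15 in the reference group. Outcomes (2.4) lists the non-microbiome secondary outcomes, which I take to be the clinical outcomes: BMI z-score at 1 and 3 months, and total body fat percentage by DXA at 3 months.

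**The concern.** An analysis set of randomised participants contains two groups. It cannot supply a difference among three. Either the population sentence or the tested-quantity sentence therefore does not describe the treatment evaluation, and the paragraph does not say which.

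The conflict matters because the third group differs from the other two by birth mode and by everything that leads to an elective caesarean, not by the intervention. The Background cites a study of faster weight gain in caesarean-born infants by 3 months and another of higher mean BMI at 6 months, while also saying that the evidence on obesity is not consistent. A birth-mode difference in these outcomes is thus something the authors themselves regard as possible. If it enters a test reported under treatment effects, a birth-mode finding could be taken for a seeding finding. The randomised contrast is the trial's only unconfounded evidence on seeding, and it is the one comparison this paragraph does not name.

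**Working it through.** The article gives no power or error figure for the clinical outcomes, so there is none to reproduce. The 85% power in Sample size is for the primary outcome and is not an input here.

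**Inputs**
- Group sizes: 15 seeded, 15 placebo, 15 vaginal-born (Sample size).
- Level: 5%, two-sided (Microbial and statistical analyses).
- Seeding effect: set to zero, to see what the test does when there is nothing to find.
- Vaginal-versus-caesarean difference *d* in SD units: **an assumption**. The article gives none, so a range of 0.2 to 1.0 SD is shown.
- Normal outcomes with a common SD: an assumption.

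**Reading A: one omnibus test of the three groups**

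The group means are (0, 0, *d*) and the grand mean is *d*/3. The noncentrality is

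λ = 15 × [(d/3)² + (d/3)² + (2d/3)²] = 15 × (6/9)d² = 10d².

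The test has 2 and 42 degrees of freedom (42 = 45 − 3). The 5% critical value is 3.22, and the rejection probability is P(F′(2, 42; λ) > 3.22).

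| *d* (SD) | λ = 10d² | Rejection with zero seeding effect |
|---|---|---|
| 0 | 0 | 5.0% |
| 0.2 | 0.4 | 7.9% |
| 0.3 | 0.9 | 11.8% |
| 0.5 | 2.5 | 25.7% |
| 0.8 | 6.4 | 58.1% |
| 1.0 | 10.0 | 78.5% |

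Allowing one degree of freedom for sex (2 and 41) changes each figure by less than 0.1 percentage point. As a test of whether any group differs, these rejections are correct. As a test of seeding, they are false positives.

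**Reading B: pairwise differences from one three-group model**

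The seeded-minus-placebo contrast does not involve the vaginal-born mean. In 40,000 simulated trials per setting with no seeding effect (no sex term), it rejected as follows.

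| *d* (SD) | Omnibus test | Seeded vs placebo contrast |
|---|---|---|
| 0 | 5.1% | 5.0% |
| 0.5 | 26.0% | 5.1% |
| 0.8 | 58.2% | 5.1% |
| 1.0 | 78.5% | 4.9% |

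The simulated omnibus column agrees with the formula. The contrast holds 5% at every *d*.

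**What the randomised contrast can show**

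For two arms of 15, with λ = 30 × (d/2)² on 1 and 28 degrees of freedom and *d* now a true seeding effect, power is 26% at 0.5 SD, 56% at 0.8 SD and 75% at 1.0 SD. It is modest, as expected in a pilot, which is a reason to report the interval and not only a p-value.

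**The case against.** The strongest reply is that no omnibus test is stated. The sentence speaks of estimates and a difference that are calculated as well as tested, and an omnibus F test gives no difference to calculate. Pairwise contrasts are at least as natural a reading. On that reading the seeded-versus-placebo result is randomised, unconfounded and holds its 5% level. This stands. A reader might infer from the sentence that the plan's treatment test is confounded or has an inflated error rate; the article does not support that, because it nowhere says a contrast with the reference group will be reported as a treatment effect.

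It can also be said that the paragraph opens by tying treatment evaluation to randomised participants, so the three-group sentence may only add a reference comparison. That is possible. It does not remove the problem: the sentence follows directly on the one about treatment effects, is the only one to name a tested quantity, and does not separate the randomised contrast from the other two.

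A reader might go further and count three contrasts on three endpoints as nine tests, with a chance of 1 − 0.95⁹ = 37% of at least one false positive. That overstates it. The contrasts share groups, and simulation with all groups equal gives about 32% for independent endpoints and 25% to 29% for endpoint correlations of 0.7 to 0.5. The article does not say that all nine would be read as treatment tests, so multiplicity is not part of this point.

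Finally, detailed contrasts are often left to an analysis plan, and none is shown here. The point does not rest on missing detail: two statements in one paragraph do not fit together.

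**Conclusion.** The point holds as an inconsistency with a practical consequence. The article restricts the clinical treatment evaluation to randomised babies, names a three-group difference as what is tested, and does not name seeded versus placebo as the treatment test for BMI z-score and body fat percentage.

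The size depends on the reading. Under an omnibus reading, the chance of a significant result with no seeding effect runs from about 8% to 79% over assumed birth-mode differences of 0.2 to 1.0 SD. Those differences are assumptions, and the low end is as open as the high end. Under a pairwise reading the seeding test keeps its 5% level, and the fault is one of labelling: one randomised contrast is mixed with two observational ones.

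Only secondary outcomes of a pilot are affected. The primary outcome is defined between the two caesarean groups in Outcomes and is not touched. The point should be corrected, but it does not threaten the trial's main result.

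**What to change.** Replace the three-group sentence in Microbial and statistical analyses with two statements.

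1. For each clinical outcome, the treatment effect is the sex-adjusted seeded-minus-placebo difference, with its 95% confidence interval, in the 30 randomised babies by intention to treat. This is the only treatment test for that outcome.
2. Comparisons of either caesarean group with the vaginal-born group are reported separately and labelled as observational reference comparisons.

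Further confounder adjustment in the second item, or leaving those comparisons untested, is a matter of preference and is not needed to resolve the inconsistency.

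The cost is wording only: no new data, no change in sample size and no change to the primary analysis. The change should be dated before the clinical outcomes are analysed by group.

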#### Patient and public involvement

2.9.9

Public input into the study design was mainly provided in open meetings by members of the Northern A Health and Disability Ethics Committee, including both clinical and lay persons, as well as Māori representatives (indigenous people of New Zealand). In addition, we have consulted with a number of healthcare practitioners in the early stages, so that feedback from obstetricians, midwives, and lactation consultants were incorporated whenever possible. However, participants have not been involved in the development or conduct of the trial.

